| X | Research subjects receiving established medical care. Hospitalization and laboratory costs paid by third party. (except for tests performed exclusively for the study) |
|  | Research subjects admitted on an industry-sponsored protocol. All costs paid by industry sponsor. Requires $2,200 IRB application and set-up fee. |

| ClinicalTrials.Gov Registration | |
| --- | --- |
| Does this study need to be registered on [www.clinicaltrials.gov](http://www.clinicaltrials.gov)? (see below) | No x Yes |
| General Requirements [U.S. Public Law 110-85](http://frwebgate.access.gpo.gov/cgi-bin/getdoc.cgi?dbname=110_cong_public_laws&docid=f:publ085.110.pdf) (Food and Drug Administration Amendments Act of 2007 or FDAAA), Title VIII, Section 801 mandates that a "responsible party" (i.e., the sponsor or designated principal investigator) register and report results of certain "applicable clinical trials":   - **Trials of Drugs and Biologics:** Controlled, clinical investigations, other than Phase I investigations, of a product subject to FDA regulation; - **Trials of Devices:** Controlled trials with health outcomes of a product subject to FDA regulation (other than small feasibility studies) and pediatric post-market surveillance studies.   "Applicable clinical trials" generally include interventional studies (with one or more arms) of drugs, biological products, or devices that are subject to FDA regulation, meaning that the trial has one or more sites in the U.S, involves a drug, biologic, or device that is manufactured in the US (or its territories), or is conducted under an investigational new drug application (IND). | |

| Principal Investigator’s Assurance |
| --- |

| **IRB #:  2015-042     Principal Investigator:      [name] MPH**  **Study Title:      Stay Healthy In Nature Everyday (SHINE)**  ***Return Initialed Form to (study coordinator):       Ext.***  ********************************************************************************************************************  ***CHORI STAFF***  *(NOTE: IRB staff will forward the application to the CHORI staff (1- 4) after an initial review)*  1. Sponsored Programs Office, Associate Director ([name]/[name])  2. Technology Transfer, Director -- [name], JD N/A  *([name]/[name] to check N/A if not required)*  3. V.P. Research Operations -- [name], MBA  4. Interim Executive Director and S.V.P., Research – [name]  ********************************************************************************************************************  **HOSPITAL STAFF**  *(NOTE: PI and/or Study Coordinator must circulate a hard copy of the application, consent and protocol to the following departments (5 – 9) for their review, if required.*  5. Director, CHRCO Pharmacy Services or designated Research Pharmacist N/A  (if pharmacy resources will be used)  6. Medical Director, Pulmonary Center N/A  (if Respiratory Care Services or Pulmonary Function Lab will be used)  7. Medical Director, Cardiology (EKGs, Echos) N/A  8. Other CHRCO resources, (as applicable), e.g., clinical laboratory,  diagnostic imaging (**print name and department below**) N/A  UCSF Benioff Children’s Hospital Oakland Primary Care Clinic    9. Administrative Director CRC, [name], MPH N/A  (if utilizing CTSI-PCRC resources) |

| **Summary Information** | | | | | | | | | | |  | |
| --- | --- | --- | --- | --- | --- | --- | --- | --- | --- | --- | --- | --- |
| **Age Range of Eligible Subjects:**  Subjects will include clinic patients and their guardians.  Clinic patients age 4 and older are eligible.  Patient guardians 18 and over are eligible. | | | | | | | | | | |  | |
| **Subject Population:** (Please check all that apply) | | | | | | | | | | |  | |
|  |  | | a. neonates | | X | f. minors | | |  | k. cancer patients | |  |
|  | X | | b. minorities/immigrants | |  | g. non-English speaking | | |  | l. terminally ill | |  |
|  |  | | c. normal volunteers | |  | h. students | | |  | m. wards of the court | |  |
|  |  | | d. institutionalized | |  | i. prisoners or parolees | | |  | n. pregnant women | |  |
|  |  | | e. decisionally impaired | |  | j. other | | | | | |  |
|  | **Study Type:**  If the research involves any of the following, please check all that apply. | | | | | | | | | | |  |
|  | |  | | a. Investigator-sponsored IND or IDE. A Sponsor-Investigator is an individual who both initiates and conducts a clinical trial. Regardless of funding source, the individual has the responsibilities of both a sponsor and investigator. | | | | | | | | |
|  | |  | | b. Investigational Drug (IND) | | |  | m. Investigational Device (IDE – HUD) | | | | |
|  | |  | | c. Genetic Research (DNA) | | |  | n. Vaccine Trial | | | | |
|  | |  | | d. Collection of Biological Specimens for Banking | | |  | o. Respiratory Treatments, Sleep  Studies, PFTs for clinical purposes | | | | |
|  | |  | | e. Collection of PHI (identified data) for Database | | |  | p. Gene Transfer Therapy | | | | |
|  | |  | | f. Collection of Remnant Surgical Specimens | | |  | q. Biohazardous Waste | | | | |
|  | |  | | g. Magnetic Resonance Imaging (MRI) | | |  | r. Radiation (including X-ray, DXA) | | | | |
|  | |  | | h. HIV Screening | | |  | s. HIV/AIDS Research | | | | |
|  | |  | | i. Alcohol and Drug Abuse Research | | |  | t. Controlled Substances | | | | |
|  | |  | | j. Acute Care Waiver of Informed Consent | | |  | u. Transplantation | | | | |
|  | |  | | k. Behavioral Observations | | |  | v. Deception | | | | |
|  | | X | | l. Surveys, Questionnaires or Psychological Testing | | |  | w. Audio/Videotapes or Focus Groups | | | | |

| **Data Safety Monitoring: *All interventional studies involving greater than minimal risk must include a Data Safety Monitoring Plan (DSMP).*** A DSMP is a plan established to assure that each research study has a system for appropriate oversight and monitoring of the conduct of the study to ensure the safety of participants and the validity and integrity of the data. The DSMP should indicate specifically whether there will be a formal Data Safety Monitoring Board (DSMB) or Data Monitoring Committee (DMC).  **All Investigator-sponsored IND or IDE studies must have a DSMP, including an SOP for data monitoring.** | | | | | | | | | |  |
| --- | --- | --- | --- | --- | --- | --- | --- | --- | --- | --- |
| Has a Data Safety Monitoring Plan been established to review data and/or adverse events related to this study? | | | | | | | X N/A (minimal risk)  Yes No | | |  |
|  | Describe the DSMP below: | | | | | | | | |  |
|  |  | | | | | | | | |  |
|  | **Research Sites:** Except for multi-center clinical trials (e.g., industry, COG) list all sites in which the research is to be conducted and attach other IRB approval letters. If applicable, attach letters of support from those institutions. X N/A – Multi-center clinical trial | | | | | | | | |  |
|  |  | | | | | | | | |  |
|  | **Investigational drugs/devices:** If any investigational drugs or biologic agents are used in this study, please include two copies of the Investigational Drug Information or Investigator’s Brochure (IB) with this application.  **X N/A IB Number:      Version Date of IB:**  **Complete and attach the following IRB forms (on the website) as applicable:**  **Study Review - Investigational Drug Information**  **Study Review - Investigational Device Information** | | | | | | | | |  |
| Protocol Summary | | | | | | | | | |  |
| **Protocol Version Date:       Amendment #:**  **Protocol Number:       N/A (no number)** | | | | | | | | | |  |
| Please complete the requested information in the categories below. If the item does not apply to your research, please indicate that the question is not applicable. The information should be intelligible to IRB reviewers from a variety of lay and scientific backgrounds. | | | | | | | | | |  |
| **Hypothesis:** Briefly explain the hypothesis(es) to be tested. If the study is not designed to test a hypothesis, simply state “None.” | | | | | | | | | |  |
| The SHINE study is a randomized controlled study of the effect of a park-based family support group on multiple outcomes (including stress and physical activity) in a low income population.   1. Primary hypothesis:   Children and caregivers enrolled in the SHINE program will have improved stress compared to those who are not enrolled in the SHINE program.   1. Secondary hypotheses:   Children and caregivers enrolled in the SHINE program will have improved social support, family functioning, physical activity, park visitation, and nature affinity compared to caregivers not enrolled in the program.  Children with obesity, ADHD, and asthma who participate in the SHINE program will show improvements in their symptoms.  The effect of the SHINE intervention will vary depending on the baseline life stressors present in the caregiver or child (the effects of nature interact with baseline stress and are dose dependent) and the dose of nature received.  During a SHINE outing, participants will experience immediate improvements in stress and 30 minutes of moderate-to-vigorous physical activity. | | | | | | | | | |  |
| **Purpose of the study:** What are the specific scientific aims of this study? | | | | | | | | | |  |
| Aim1: To determine changes in stress, social support, family function, physical activity, park visitation, and nature affinity amongst primary care patients ages 4 and older, and their caregivers enrolled in the SHINE intervention compared to those in a control group.Aim 2: To determine changes in BMI, ADHD symptoms, and asthma control for patients enrolled in the SHINE program compared to those who are not.Aim 3: To assess immediate changes in stress and minutes spent in moderate-to-vigorous physical activity by enrolled patients and their enrolled parents during SHINE outings. | | | | | | | | | |  |
| **Background and Significance:** Include a brief summary of previous work that provides a basis for the proposed research and that supports the expectations of obtaining useful information without undue risk to human subjects. **Provide a Bibliography (References)**  This information aids IRB reviewers in assessing how valuable the project is likely to be. If graphs or tables are used to convey information, please maintain a consistent style and make sure that fonts are no less than 11-point in size. If no preliminary data are available, it may be helpful to indicate briefly why this proposed study is a reasonable starting point. Note that some IRB members are non-scientists and may not be familiar with scientific or technical terms. | | | | | | | | | |  |
| Families served by UBCHO Primary Care Clinic experience high levels of stress (Children’s Hospital Community Needs Assessment, 2013). As a safety-net clinic, UBCHO PCC serves a diverse set of patients, with a common thread of poverty (Children’s Hospital Community Needs Assessment, 2013). Without intervention, stress can lead to a variety of physical and mental health morbidities (Brotman, Golden and Wittstein, 2007) (Bovier, Chamot and Perneger, 2004) (Marin, et al. 2011).  Local parks have the potential to serve as an affordable, community-based resource in stress management for low-income communities in that they can provide families with an opportunity to be with friends and family in nature.  Nature has been shown to buffer the effects of stress on health. Like other protective factors, such as a caring adult, safe play places, greater stimulation, the presence of greenspace has been empirically linked to greater resilience (Bradely et al. 1994). Nancy M. Wells and Gary W. Evans showed in 2003 that nature acts as a buffer or moderator, mitigating the impact of stress on adversity on children - in other words the presence of a natural environment attenuated the adverse effects of strayers or other adverse main effects on health or well-being. In a study of 337 children in 3-5th grade, they found that socio-economic status was positively related to children’s self-worth (F 15.86, p<0.001), there was a main effect of nature such that the higher nature corresponded to higher self worth.  Factors that contribute to nature’s buffering effect on stress include social cohesion and support, physical activity, and improved attention when groups are in nature.  Increased social cohesion has been shown to be a mediator in the overall pathway linking exposure to nature to an increase in health benefits (Sjerp de Vries, et al. 2013). The tie linking green spaces and improved social cohesion is well documented. In one study, 83% more social activities were found to occur in green spaces than in barren ones with twice as many people using the green versus barren spaces (Sullivan, Kuo and al 2004). In another, green spaces were shown to be more supportive of children’s play and gave them more intergenerational interaction with adults, including non-family members (Faber Taylor and Wiley 1998). These and other studies suggest that green spaces serve as social magnets, bringing people together in a natural environment where social interaction and community building can organically occur.  Research to date suggest that participation in outdoor activities facilitates a sense of interconnectedness with nature (Scott, Amel and Manning 2014). This sense of attachment, we postulate, may also provide a form of social support.  Time outdoors in natural spaces is associated with increases in physical activity. One study, for example, found that for every additional hour spent outdoors, physical activity increased by 27 minutes a week and the prevalence of overweight decreased by 41% to 27% (Cleland, et al. 2008). Physical activity, in turn, lesses anxiety and depression, lower rates of obesity, and improved cardiovascular functioning (US Department of Health and Human Services 2008). | | | | | | | | | |  |
| **Study Design:** (Check all that apply). | | | | | | | | | |  |
| Placebo | | | Blinded | X Randomized | Investigational intervention without random assignment | | | | |  |
| If this study has any of the formal designations below, please indicate below: N/A | | | | | | | | | |  |
| Phase I | | | Phase II | Phase III | Phase IV | Open Label Extension | | | |  |
| Additional description of general study design. Sequentially list all procedures, drugs or devices to be used on human subjects. Describe any use of placebos and indicate whether subjects will be randomized in this study. Attach flow diagram if appropriate. **If there are any investigational drugs, devices or biologic agents used in this study, complete and attach the FDA Form 1572.** If this is an investigator-initiated study, attach the FDA Investigational Drug Application (FDA Form 1571). | | | | | | | | | |  |
| To evaluate specific aims 1 and 2, the study design uses a randomized controlled trial design.  Potential participants will be given a short description of the study (Please see attached waiver to screen patients). If they agree to be screened, they will be screened for eligibility using a short screening tool.  If they are eligible based on the screening tool, they will consented and enrolled. All enrolled participants (which includes a caregiver and a child per family), will receive:   - Resources to find local parks - A recommendation to be physically active three times a week - A pedometer with a diary to record their daily steps - Three tubes for salivary cortisol collections   They will be asked to:   - Complete a questionnaire - Collect a first morning salivary cortisol during the first week, fourth week, and twelfth week of participation - Return to clinic to complete a questionnaire, and to have their child’s BMI measured, on the fourth week and twelfth week of participation - Turn in their physical activity logs on the fourth and twelfth week visits   Upon completing the baseline measures, participants will be randomized to one of two treatment groups ('A' or 'B') by a computer program (we will use Redcap) and the result recorded. Randomization will be blocked (using random permuted blocks) to ensure that the groups are balanced periodically.  The control group will have no added activities.  The intervention group will be asked to return to clinic on the first, second, and third week of the study at 1 pm - 4pm on Saturday. During these visits, they will meet with clinic staff as well as with other participating families. They will turn in their physical activity logs for a week. They will then board a school bus and travel to one of three local parks (Week 1 = Crab Cove, Week 2 = Temescal Lake, Week 3= Redwood Regional Park). Once at park, they will experience:   1. A warm welcome and ice breaker games 2. 30 minutes of lunch and unstructured play 3. 60 minutes of light walking   They will journal about their outdoor experiences. The journal will include questions about stress and well-being.  The intervention group will also be encouraged to visit a park or be physically active at least three times a week every week for six weeksand will be able to chronicle their outdoor physical activity in their journal.  To assess Aim 3 we will survey only the families in the intervention arm:  During the third SHINE outings, enrolled guardians and children will be invited to wear an accelerometer for the duration of the event. Accelerometers will be programmed to record data in 15-second intervals and will allow us to calculate minutes spent in moderate to vigorous physical activity. Participants will return their accelerometers prior to boarding the shuttles to return home. | | | | | | | | | |  |
| Study Population | | | | | | | | | |  |
| **Characteristics of the Subject Population:**  Describe the gender, ethnic background and health status. Provide a candid discussion of potential problems, if any, related to the study population. Explain the rationale for the use of special classes such as pregnant women, children, prisoners, wards of the court, or other vulnerable populations. If women, minorities, non-English speaking subjects or children are excluded, provide written justification. | | | | | | | | | |  |
| The target population for this study are low income children and caregivers. The study population are UCSF Benioff Children’s Hospital Oakland Primary Care (UBCHO PCC) patients ages 4 and older, and a caregiver. The study population approximates the target population as 95% of patients live within 300% of the federal poverty level. We will be looking at children above age three in order to assess physical activity. Our study population excludes physically disabled patients because we are following physical activity as an outcome.  UBCHO PCC patients are very diverse, with African American and Latino patients comprising more than half of the patient population. UBCHO patients are linguistically diverse, with 58 reported languages; one in five patients speaks a language other than English. Spanish is the second most common reported language after English. For this reason, we will be translating all SHINE materials into Spanish, and we will have Spanish speaking park personnel available during all outings at the parks. Arabic speaking patients are also increasing in numbers at UBCHO Primary Care Clinic. As our research assistant [name] is a fluent Arabic speaker, she will be of assistance in ensuring that this population is not excluded. | | | | | | | | | |  |
| **Inclusion/Exclusion Criteria:** Indicate the criteria for exclusion and inclusion and explain the system for equitable selection of subjects. | | | | | | | | | |  |
| Our system for equitable selection of study patients is to use a screening tool that will ensure systematic enactment of our inclusion and exclusion criteria.Inclusion criteria are: the adult must be the legal guardian, at least 18 years old and familiar with the child’s health. The enrolled child must be at least 4 years old. This age cut-off for participating children was chosen because of programming considerations once the families are in the parks and in order to measure physical activity in the child. Because we are measuring physical activity, the caregiver and child need to have no physical disabilities that would limit their ability to be able to be physically active.  Both caregiver and child must be willing to be randomized, and must be available for follow up over the next 3 months. If they are randomized to the intervention group must return to clinic weeks 1, 2, 3 on Saturdays for group park visits, as well as to visit parks on their own for six weeks. | | | | | | | | | |  |
| 1. **Eligibility for Study:** How is eligibility determined and by whom? | | | | | | | | | |  |
| Eligibility for the study will be determined by the research coordinator by reading through the eligibility screen with referred patients and their guardians. All answers to the eligibility questions must be yes. If any of them are no, the patient will not be eligible. Any questions will be discussed with the study coordinator [name] or by the PI, [name]. | | | | | | | | | |  |
| 1. **Duration of Subjects' Participation in the Study (include follow-up if applicable):** | | | | | | | | | |  |
| Patients will be enrolled for a total of 12 weeks. They will participate in a survey at the time of randomization, at one month out from the beginning of the study, and three months after the end of the intervention. | | | | | | | | | |  |
| Enrollment Plan and Recruitment | | | | | | | | | |  |
| 1. **Planned Enrollment at CHRCO:**  Number of subjects needed to complete the study. | | | | | | | | 200 total participants (100 families with 1 adult and 1 child enrolled in each family) | |  |
| **Enrollment plan:** If you expect failed screenings or subject withdrawals, will they be replaced until the appropriate numbers of subjects have completed the study? If No, explain below. | | | | | | Yes XNo N/A | | | |  |
| We need 200 participants (100 parent/child dyads) in order to complete this goal. In order to enroll this number, we anticipate screening 300 participants (150 parent/child dyads) for eligibility, enrolling 240 participants (120 parent/child dyads) and having 200 participants (100 parent/child dyads) participate in the programing.  If a subject fails a screening, we will keep record of their screening, and will continue screening until appropriate subjects have enrolled in the study.  Because our intervention arm has park outings that occur at a set time (either in July, August, or September), we may not be able to replace all subject withdrawals. We will have the option of increasing the number of participants in later sessions if the first session is under-enrolled. | | | | | | | | | |  |
| **Recruitment:** What methods will be used to identify and recruit potential subjects? Attach a copy of all planned advertisements, flyers and letters, etc. to potential subjects. | | | | | | | | | |  |
| Recruitment will occur through provider referral and self-referral. In order to advertise the study:We will present at staff meeting for health care providers. Potential participants referred by health care providers will be called by the research assistant.The research assistant will be present in the clinic waiting room during the first two weeks of each month.[name], the research coordinator or research assistant will approach patients who are waiting for their appointment, will describe the project, and ask their interest in being involved.Patients will be allowed to self-refer. A recruitment flier will be placed in the waiting room with the study coordinator’s phone number listed  - Patients will be given the opportunity to consent right there and then, or will have the opportunity to go home, consider, and call back later for screening/consent. | | | | | | | | | |  |
|  | Informed Consent | | | | | | | | |  |
|  | 1. **Capacity to Consent:** Will all subjects have the capacity to give informed consent? If not, describe the likely range of impairment and explain how, and by whom, their capacity to consent will be determined. | | | | | | | | |  |
|  | Potential participants will be screened for eligibility prior to consent. We have submitted a request to waive screening prior to screening for eligibility. A short description of the study will be given prior to completing the consent form. This way, we will minimize the time burden placed on potentially interested families. In addition, the eligibility criteria limits participating caregivers to those who are also the child’s legal guardian. These individuals are also in charge of the child’s medical decision making and will be able to consent for the child. It will be clear that the legal guardian is expected to accompany the child on park outings and on follow up visits.  If they are eligible and interested, all subjects will have the capacity to give informed consent in English, Spanish, or Arabic. If they require assistance in another language, an interpreter will be called. After a summary of the protocol is given, the participant will be asked by the study personnel to summarize their understanding of the study, and whether they have any questions.  The adult participant will be giving consent for themselves and for their child. Children above 13 will also sign the informed consent form. Children ages 7 - 13 will have the study described to them (they will be read an assent form, submitted with this application), and will give a verbal assent.  The subject’s capacity to give consent will be determined by the person administering the eligibility screen and consent discussion. This will be our research assistant, our research coordinator, or the principal investigator. Each of these individuals is trained and experienced in interview techniques. Any questions or grey areas will be discussed with the principal investigator. | | | | | | | | |  |
|  | 1. **Translation of Consent Form:** If you anticipate that more than five (5) subjects in the study population will speak/read a single language other than English, the IRB-approved English language consent form must be translated according to IRB policy. Please indicate below into what language(s) the consent form will be translated, and the method of translation you are requesting. | | | | | | | | |  |

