|  | The benefits of this study include:   - The potential to learn about parks and local natural resources. - Receiving advice and support in becoming more physically active. - The potential to develop friendships and social support with other study participants. - Scientific discovery of the health benefits of nature potentially facilitating funding of future programs to benefit similar families. | | | | | | | | |  |
|  | 1. **Therapeutic Alternatives:** What therapeutic alternative(s) are reasonably available to potential subjects should they choose not to participate in the study? These may be research or non-research based alternatives. | | | | | | | | |  |
|  | Caregivers or children who are noted to report high levels of loneliness, stress, or family dysfunction will be referred to existing services through the behavioral health department at UCSF Benioff Children’s Hospital Oakland. If any acute psychosocial issues are noted, they will be referred to the social worker on call. Patients in the control arm will have access to the Family Information and Navigation Desk as well as to East Bay Regional Park District resources if they seek assistance in arranging for outdoor physical activity experiences. | | | | | | | | |  |
|  | **Financial Considerations** | | | | | | | | |  |
|  | 1. **Payment for Participation:** Describe all plans to compensate subjects, including provision of services, and other reimbursements. Describe the conditions that subjects must fulfill to receive full or partial pro-rated payment. | | | | | | | | |  |
|  | - Participating families will receive $20 for completing the baseline survey, $40 for completing the second survey, and $40 for completing the final survey. This will result in $100 compensation for their time during the duration of the study. Please note that this incentive is per family, and not per participant. - Each participating caregiver will receive a pedometer. - Each participating child will receive a pedometer. - Families in the intervention arm will receive a lunch during the park outings. | | | | | | | | |  |

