| We will examine differences in outcome variables between the guardians participating in the SHINE intervention and the control group and will stratify by age, If caregiver stress improves for participants in SHINE intervention decreases more than guardians in the control arm, we infer a functional relationship between the SHINE intervention and guardian stress.  We will present descriptive statistics of baseline covariates using means and proportions.  Our primary outcome (guardian stress) is measured by the PSS score, a continuous repeated measure. Because this study uses a randomized control design, we will use ANOVA procedures to estimate the effect of SHINE. We will also adjust for possible empirical confounding by incorporating covariates with a bivariable association with the primary outcome (guardian stress) into a multivariable ANOVA model.  Analyses will also explore potentional interaction that correspond to amount of pre-existing life stressors or ACE score, and nature exposure and the effect of SHINE on stress. We will estimate the degree to which measures of pre-existing stress account for the effects attributed to the particular SHINE.  .  Secondary outcomes of interest (child stress, BMI, ADHD score, asthma score) are also continuous measurements and will be analyzed using ANOVA procedures or other appropriate multivariable models accounting for correlations due to repeated measurements. We will also adjust for possible empirical confounding by incorporating covariates with a bivariable association with the secondary outcomes.  Aim 3. We will examine changes in stress, and minutes spent in moderate to vigorous physical activity duringhe SHINE intervention for participating guardians and children.  We will present changes in these continuous variables using a paired-t test.  Power Analysis  We calculated the power to detect differences of 0.5 effect size between the intervention and control group. With a type I error of 0.05, and a Type II error rate of 0.20, and a two-tailed statistical test.  Attrition and Missing Data  We expect 20% attrition among participants, and we do not expect participant attrition to vary by treatment condition - those receiving the intervention may have higher attrition than others. Both groups have the inconvenience of coming into clinic. One group has the extra time to spend, but it is also a bigger commitment. In light of attrition, however, we will attempt to identify key predictors of attrition status, such as [example predictors, e.g., SES, reading level], and test for differences between conditions. Our plan to deal with missing data is to analyze patients as intent to treat and will check for the impact of missing data using sensitivity analysis. |

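### SHINE is delivered to groups of families, but the primary ANOVA and the power calculation make no allowance for correlation within a SHINE group; if there is any, the standard error is understated.

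*Protocol*

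**What the plan says.** The Hypothesis section describes the trial as testing the "effect of a park-based family support group on multiple outcomes". Under Study Design, randomisation is by family in permuted blocks. SHINE families come to the clinic on three Saturdays, where "they will meet with clinic staff as well as with other participating families". They then share a bus, games, a meal and a walk. For the other arm, "The control group will have no added activities".

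The Enrollment plan places the SHINE arm's "park outings that occur at a set time (either in July, August, or September"). It keeps open the option of "increasing the number of participants in later sessions if the first session is under-enrolled", so sessions are separate cohorts of adjustable size. The Benefit Ratio section counts as a benefit "The potential to develop friendships and social support with other study participants".

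For the primary outcome, guardian PSS, the Statistical Analysis section says "we will use ANOVA procedures to estimate the effect of SHINE". A second version adds covariates that show a bivariable association with the outcome. The only correlation named is that between repeated measurements, and it is named in the text on secondary outcomes. The power paragraph gives an effect size of 0.5, two-sided alpha 0.05 and 80% power. Session, outing group and ICC appear in neither place.

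**The concern.** When one arm is treated in groups and the other is not, outcomes in the treated arm can share a group component: the same companions, staff, bus, weather and group atmosphere. An ANOVA that takes families as independent counts this shared component as if it averaged out over all SHINE families. It averages out only over the groups, and there may be as few as three.

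The protocol itself gives reason to expect some correlation. Its Background section treats social cohesion as a route from nature to health, and improved social support is a secondary hypothesis. If families influence one another as intended, their stress scores will tend to move together.

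At stake are the width of the confidence interval for the primary result, the false-positive rate of its test, and the power on which the sample size rests.

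**Working it through.** **The plan's own figure.** From 0.5 SD, two-sided 0.05 and 80% power, n per arm = 2 × (1.960 + 0.842)² / 0.5² = 62.8, so 63 per arm or 126 families. The plan states 100 families, which gives about 70% power at 50 per arm. That mismatch is a separate matter. It shows here only that the stated inputs contain no design effect.

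**Inputs for the check**
- 120 dyads enrolled (Enrollment plan) and 20% attrition (Attrition and Missing Data): 120 × 0.80 = 96 analysed families.
- Assumed 1:1 allocation (the ratio is not stated): 48 per arm.
- Assumed one outing group in each of three sessions: 48 / 3 = 16 families per group. The number of groups is not stated.
- ICC in the SHINE arm: not stated, so a range of 0 to 0.05 is assumed. Controls are taken as independent.

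**Formulae**
- Design effect in the SHINE arm: DE = 1 + (m − 1) × ICC, with m = 16.
- True SE / ANOVA SE = sqrt((DE + 1) / 2), because only one of the two equal arms is inflated.
- Type I error = 2 × (1 − Φ(1.96 / ratio)).
- Power at 0.5 SD = Φ(0.5 / SE − 1.96), with SE = sqrt(2 / 48) × ratio = 0.204 × ratio.

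| Assumed ICC | DE | True SE / ANOVA SE | Type I error | Power with correct SE |
| --- | --- | --- | --- | --- |
| 0 | 1.00 | 1.00 | 0.050 | 0.69 |
| 0.01 | 1.15 | 1.04 | 0.059 | 0.66 |
| 0.02 | 1.30 | 1.07 | 0.068 | 0.63 |
| 0.05 | 1.75 | 1.17 | 0.095 | 0.55 |

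Worked line for ICC 0.05: DE = 1 + 15 × 0.05 = 1.75; ratio = sqrt(2.75 / 2) = 1.17; 1.96 / 1.17 = 1.67, which gives 0.095.

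**Simulation.** With 20,000 runs and three groups of 16, the unadjusted t-test rejected in 5.1 / 5.9 / 6.5 / 9.4% of null trials at these four ICCs. Multiplying the SE by the ratio above brought this back to 5.1 / 5.0 / 4.8 / 5.2%.

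**Smaller groups.** With m = 8 (six groups) and ICC 0.05, DE = 1 + 7 × 0.05 = 1.35, the ratio is sqrt(2.35 / 2) = 1.08, and type I error is about 7%.

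**Does a fixed session factor help?** In the same simulation, adding session as a fixed factor in both arms gave rejection rates of 5.1 / 5.9 / 6.5 / 9.6%, which is no improvement. The factor removes what the two arms share in a session. The problem lies in what only the SHINE families share.

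**The case against.** Four points can be made in the plan's defence.

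1. **No ICC is given, and it could be close to zero.** Group contact is three Saturday afternoons. The rest of the programme is independent visits, allocation is by family, and the outcome is self-reported stress at one and three months. This stands. At ICC 0 nothing is wrong, and at 0.01 the effect is slight.
2. **Silence is not a statement of independence.** A statistical analysis plan may add a group term, and that document is not at hand. This stands for the model. It does not cover power: the sample size and the effect-size inputs are fixed in the protocol, and a later model cannot recover power lost to clustering.
3. **The number of groups is unknown.** Three is inferred from three months. More and smaller groups would shrink the effect, as the calculation for groups of 8 shows. This stands.
4. **Calendar effects.** A reader might infer that a good or bad month could pass for a programme effect. The documents do not support that. Permuted blocks keep the arms balanced over time, so each session has concurrent controls. A month effect common to both arms neither biases the contrast nor narrows the interval wrongly. In simulations with 50 per arm and a shared session ICC of 0.05 and 0.10, type I error was 0.045 and 0.043, slightly conservative.

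**Conclusion.** The concern holds in conditional form. Group delivery in one arm is documented, and neither the named primary analysis nor the power inputs allow for it. If guardian PSS scores correlate within a SHINE group, the standard error is understated and power is overstated.

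Under three groups of 16 and ICC 0 to 0.05, the true standard error is 0 to 17% larger than the ANOVA's. Type I error runs from 5% to about 9.5%, and power at 0.5 SD falls from 0.69 to 0.55. The size rests on the assumed ICC, the assumed number of groups and 1:1 allocation. Most of the gap to 80% power is there before any clustering.

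It would be tempting to say outright that the trial's error bars are too narrow. The documents do not establish this, because they give no ICC. They establish only that the plan has no protection if the ICC is positive, which its own rationale makes plausible.

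**What to change.** - Record the outing group for every SHINE family.
- Prespecify a sensitivity analysis of the primary outcome that allows clustering in the SHINE arm only, with each control family as its own cluster.
- About three groups leave only about 2 degrees of freedom for the group variance, so that model alone will be unstable. Also report the confidence interval with the standard error multiplied by sqrt((DE + 1) / 2) over ICC 0 to 0.05, using the actual group sizes.
- Restate power over the same ICC range.
- Optionally, add session as a fixed factor for precision and show the effect by session. This should not be presented as a correction for the one-arm clustering.

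The cost is one extra data field, some wording and a few lines of code. The downside is a wider interval in the sensitivity analysis and a lower stated power. No trial procedure changes.
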